## 3. Materials and Equipment

To develop the protocol, patients with sleep apnea were included who underwent submental cervical ultrasound and DISE before starting the AirwayGym App and after 3 months of treatment.

The measurements were made with the convex probe of the FUJFILM Sonosite LX ultrasound.

In submental ultrasound in the context of sleep apnea, different parameters can be measured to evaluate the size and function of the genioglossus and geniohyoid muscles, which are important for keeping the upper airway open during sleep. Some of the parameters that can be measured in submental ultrasound are:Genioglossus and geniohyoid muscle thickness: The thickness of the genioglossus and geniohyoid muscles can be measured at different points on the lower part of the jaw. A smaller thickness may indicate weakness or atrophy of these muscles.The cross-sectional area of the genioglossus and geniohyoid muscles: The cross-sectional area of the genioglossus and geniohyoid muscles can be measured at different levels of the lower jaw. A smaller cross-sectional area may indicate a decrease in the size of these muscles.Tongue movement distance: The tongue movement distance forward from the rest position can be measured. A shorter movement distance may indicate weakness in the muscles that control the position of the tongue.

## 4. Detailed Procedure

Inclusion criteria (patients):Ages of 18–75 years;Diagnosis of moderate–severe OSA (AHI > 15);Not having used any previous treatment other than that in this study or lasting longer than 3 months in the case of the control group;Signature of informed consent (IC);Present good permeability and nasal function;Body mass index (BMI) of <30.

Exclusion criteria for both:
Cognitive or neurological deficit;Inability to complete questionnaires;Severe alcoholism;Presence of craniofacial malformations;Active neoplastic disease;History of previous rehabilitation treatment of the orofacial musculature as well as any other treatment for previous apnea that could modify the results of this study (e.g., surgery or a mandibular advancement device (M));Temporomandibular joint dysfunction;Ankyloglossia of the tongue or inability to perform MT exercises;Not having a smartphone, or being unable to use it, or an Internet connection at home;BMI of >30;Weight changes with an increase of >5 kg during the 3 months of study.

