## 2. Experimental Design

This is a nonsponsored prospective, non-randomized pilot study coordinated by the Pulmonology, Anesthesiology, and Otolaryngology Departments of Quirónsalud Marbella Hospital and Campo de Gibraltar Hospital, Andalucia, Spain. This study has been registered (ISRCTN92645461) and approved by the local ethics committee (AWGAP20232).

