### 2.2. Study Groups

The control group will include patients with recent moderate–severe sleep apnea (1–3 months) undergoing treatment with continuous positive airway pressure (CPAP) therapy. An initial ultrasound measurement of the tongue genioglossus fat will be made and 3 months after inclusion in this study.

The MT group will include patients with moderate apnea. MT exercises alone, once a day for 3 months, will be performed exclusively via the AirwayGym app. An initial ultrasound measurement and drug-induced sleep endoscopy (DISE) will be performed with repeated control at 3 months.

In the MT-CPAP severe apnea group, patients will use CPAP at night, measuring the number of hours they use it at night. A new sleep study will be performed at 3 months. An initial ultrasound measurement and DISE will be made with control at 3 months (Figure 1).

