### 2.3. Objectives

-To evaluate the influence of MT on the reduction in cervical fat and the improvement of ultrasound parameters in sleep apnea.-To measure different parameters related to the function and size of the genioglossus and geniohyoid muscles to evaluate the presence and severity of sleep apnea, as well as the effectiveness of myofunctional therapy in improving the function of these muscles.-To determine whether performing a neck ultrasound is relevant for the indication of TM in sleep apnea.-To evaluate whether performing ultrasound and DISE modify the indication of surgical techniques compared with if we only performed DISE.-To evaluate the adherence to CPAP and MT.

The hypothesis of our work is based on determining whether knowledge of the fatty and muscular components can be decisive in the choice of pharyngoplasty techniques, in multilevel surgery, and as a possible predictor of response or failure to MT since, currently, the influence that TM can have on reducing cervical fat is unknown.

Given that the aforementioned tools only measure strength, we consider the previous study of cervical fat using ultrasound and its response to TM relevant in the study of collapse patterns during DISE.

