### 4.1. Sample Size

Calculation of sample size

No studies have reported on the influence of MT on the reduction in cervical fat in patients with sleep apnea and evaluations of obstruction patterns in DISE before and after. Our study will initially be a pilot study, with 15 patients in the control group, 15 patients in the moderate MT apnea group, and 15 patients with MT-CPAP severe apnea.

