### 4.3. Assessments

Patients will be jointly evaluated by the pulmonology and otorhinolaryngology services of the hospital.

Evaluation by a pulmonology specialist: A detailed medical history is taken to record symptoms and risk factors associated with sleep apnea. BMI is calculated, and questionnaires that assess daytime sleepiness (the Epworth test; Appendix A) and sleep quality (the Pittsburgh questionnaire; Appendix B) are administered. Patients suspected of having sleep apnea undergo either polysomnography or diagnostic respiratory polygraphy based on their clinical symptoms. After this first assessment, the pulmonologist refers the patient to the otorhinolaryngology department to assess the anatomy and functionality of the upper airways. Patients with a BMI of >30 are transferred to the nutrition and dietetics unit. It is known that a reduction in BMI of 5–10% significantly reduces the AHI [32].

The sleep study is performed using standard polysomnography.

Standard nocturnal polysomnography involves (i) recordings of sleep-related electroencephalography (EEG), electromyography (EMG) of the chin and leg muscles, electrooculography (EOG), and electrocardiography (ECG); (ii) oxygen saturation; and (iii) measures of respiratory effort and airflow.

The tests are used to define PS with an AHI of <5 events/h of sleep, moderate OSAHS as an AHI of 15 to 29.9 events/h of sleep, and severe OSAHS as ≥30 events/h of sleep [eleven].

Laboratory-assisted polysomnography has been and continues to be a gold standard for the diagnosis of sleep-disordered breathing, although the usefulness of a single night-time recording for diagnosis can generate considerable variability in the AHI from night to night, especially when the AHI is low [11].

Therapy with the AirwayGym^®^ application will be initiated after inclusion in this study. This therapy will be applied to patients with an average duration of training of 5 days a week with 15–20 min/session. Three months after myofunctional therapy, an otorhinolaryngological evaluation, sleep questionnaires, and tongue strength measurements with the IOPI and ultrasound will be performed [11].

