The distribution of visits to the center will be as follows:Pulmonology visit: Patients will be diagnosed with OSA in a pulmonology laboratory via an initial sleep study, which includes the measurement of baseline AHI, the nocturnal desaturation index, and the lowest oxygen saturation levels during the night.Otorhinolaryngology visit: Patients will be assessed by the otorhinolaryngologist, who will evaluate the anatomy and functionality of the upper airways using DISE and measure tongue strength with the IOPI and TDS. The AirwayGym app is recommended for patients with oropharyngeal hypotonia.Ultrasound visit: A neck ultrasound will be performed to measure tongue thickness (mm), height (mm), volume (cm^3^), and distance between the lingual arteries (mm) before DISE and at the start of treatment modulation with the app (Figure 4 and Figure 5).Monthly telemedicine follow-up: During the 3-month study period, all patients in the three groups will be monitored for adherence and incidents related to the prescribed treatment with the AirwayGym app.Three-month follow-up: All variables evaluated during the initial visit will be measured again after three months. The ultrasound visit is an evaluation added to this previously published protocol (Tongue +) [36]. A submental ultrasound will be performed in the context of sleep apnea.

The Kolmogorov–Smirnov test will be used for the distribution of quantitative variables. The chi-square test or Fisher test will be used as necessary for the study of categorical variables. Student’s *t*-test or ANOVA (for two or more samples) will be used to study the differences between quantitative variables.

Non-parametric tests (Mann–Whitney or Kruskal–Wallis) will be used if the variables to be analyzed do not follow a normal distribution. The level of statistical significance will be set at *p* < 0.

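### Excluding patients who gain more than 5 kg during the study, while keeping those who lose weight, can modestly flatter within-group change in fat-related measures

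*Protocol article*

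**What the plan says.** Section 4 (Detailed Procedure) of the protocol article includes this item in its exclusion list: "Weight changes with an increase of >5 kg during the 3 months of study". No item in that list, and nothing elsewhere, excludes weight loss during the study.

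The first objective in section 2.3 is "To evaluate the influence of MT on the reduction in cervical fat and the improvement of ultrasound parameters in sleep apnea". Section 4.2 lists weight and BMI among the collected variables. Section 4.3 says of the follow-up visit: "All variables evaluated during the initial visit will be measured again after three months". Section 2.2 says, for the MT-CPAP group, "A new sleep study will be performed at 3 months". Section 4.3 also remarks: "It is known that a reduction in BMI of 5–10% significantly reduces the AHI".

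The design in section 2 is described thus: "This is a nonsponsored prospective, non-randomized pilot study". Section 4.1 plans "15 patients in the control group, 15 patients in the moderate MT apnea group, and 15 patients with MT-CPAP severe apnea". The tests at the end of section 4.3 are t-test or ANOVA, or rank-based equivalents, with no adjustment for weight stated. The article does not say whether patients who meet the weight criterion are withdrawn, replaced, or only left out of the analysis.

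**The concern.** An eligibility criterion should be assessable at entry. This one depends on what happens over the following three months, so it removes patients who are already enrolled and under treatment. It is also one-sided.

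Weight is a plausible correlate of what the study measures. The article itself links lower BMI to lower AHI, and its introduction names obesity and neck fat among the suggested causes of OSA. If weight gain goes with more fat and a thicker tongue, the rule takes out patients likely to show worsening and leaves in those whose improvement may come from weight loss. Mean before-after change among those kept then looks better than in all enrolled patients, even with no treatment effect. Section 5.1 already presents before-after change in lingual thickness as evidence of benefit, so this kind of comparison will be read.

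**Working it through.** The article gives no figure for weight change, so there is nothing of its own to reproduce. The check asks which way the rule moves the results, and how far.

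**Inputs from the article.** Cut-off +5 kg (section 4); 15 patients per group, 3 × 15 = 45 in all (section 4.1).

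**Assumptions, not in the article.** Weight change W over 3 months is normal with mean μ of 0 to 2 kg and SD σ of 2 to 5 kg. Its correlation r with change in a fat-related outcome is 0.3 to 0.5.

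**Formulas.** With a = (5 - μ)/σ:
- share dropped = 1 - Φ(a)
- shift in mean weight change among those kept = -σ·φ(a)/Φ(a)
- shift in outcome, in SDs of outcome change = r·φ(a)/Φ(a), towards improvement

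**One line worked.** μ = 0, σ = 4: a = 1.25, φ(a) = 0.1826, Φ(a) = 0.8944. Dropped: 10.6%. Weight shift: -4 × 0.1826/0.8944 = -0.82 kg. Outcome shift: 0.3 or 0.5 × 0.204 = 0.06 or 0.10 SD.

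| μ (kg) | σ (kg) | dropped | of 15 | of 45 | weight shift (kg) | outcome shift (SD), r = 0.3 to 0.5 |
|---|---|---|---|---|---|---|
| 0 | 2 | 0.6% | 0.09 | 0.28 | -0.04 | 0.005 to 0.009 |
| 0 | 3 | 4.8% | 0.72 | 2.15 | -0.31 | 0.031 to 0.052 |
| 0 | 4 | 10.6% | 1.58 | 4.75 | -0.82 | 0.061 to 0.102 |
| 0 | 5 | 15.9% | 2.38 | 7.14 | -1.44 | 0.086 to 0.144 |
| 1 | 4 | 15.9% | 2.38 | 7.14 | -1.15 | 0.086 to 0.144 |
| 2 | 4 | 22.7% | 3.40 | 10.20 | -1.56 | 0.117 to 0.195 |
| 2 | 5 | 27.4% | 4.11 | 12.34 | -2.30 | 0.138 to 0.230 |

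The weight shift is downward in every row. With μ = 1 and σ = 4, a true average gain of 1 kg becomes 1 - 1.15 = -0.15 kg among those kept.

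**Yardstick.** With 15 patients, the standard error of a group's mean change is 1/√15 = 0.26 SD.

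**Between groups.** If weight change has the same distribution in two groups, the shifts are equal and cancel. If one group gains on average 1 kg or 2 kg more than a group with mean 0 (σ = 4), the contrast in weight change is distorted by 1.15 - 0.82 = 0.33 kg or 1.56 - 0.82 = 0.74 kg, and the group that gains more looks better than it is.

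**A symmetric rule.** Dropping changes beyond 5 kg in either direction gives no shift when μ = 0. With σ = 4 and μ of 1 or 2 kg it still shifts mean weight change by -0.58 or -1.17 kg.

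**The case against.** The strongest reply is about size. At σ = 2 kg the effect is negligible, and in all the zero-mean cases the outcome shift is well inside the 0.26 SD standard error of a group of 15. This stands, and it keeps the point modest. It does not excuse the rule, because a bias with a known direction is not removed by being smaller than the noise.

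The BMI sentence in section 4.3 is weak support for size. It follows a remark on referring patients with BMI above 30, whom section 4 excludes, and it speaks of 5–10%. For an assumed patient of 70 to 90 kg, a shift of 0.3 to 1.4 kg is about 0.3% (0.3/90) to 2% (1.4/70) of body weight. The sentence supports a direction for AHI only. The link from weight change to tongue or cervical fat is inference.

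Three stronger readings are tempting and are not supported:
- A reader might infer that every tongue measure is biased towards benefit. Section 3 treats smaller genioglossus and geniohyoid size as a possible sign of weakness, and sections 1 and 5.1 expect MT to enlarge these muscles, so keeping lighter patients need not look like benefit there.
- A reader might infer that AHI change is affected throughout. Section 4.2 lists only the initial AHI, and section 2.2 names a repeat sleep study only for the MT-CPAP group. Only the general follow-up sentence in section 4.3 extends it further.
- A reader might infer that the rule favours MT over control. It does so only if the MT patients gain more weight. If the control patients gain more, it works against MT.

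The rule may be meant to limit confounding by weight gain. That aim is reasonable, but it would call for attention to loss as well as gain. It is also true that analysis sets are often left to a fuller document. Even so, placing the item under exclusion criteria implies that these patients are removed.

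**Conclusion.** The point holds in limited form. The article fixes an exclusion that depends on a post-baseline event and runs one way. Within groups it can bias before-after change in cervical or tongue fat and lingual thickness, and in AHI where it is repeated, towards apparent improvement. It has no fixed direction for muscle size or for comparisons between groups.

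For mean weight change of zero and an SD of 2 to 5 kg, the outcome shift runs from about 0.005 to 0.14 SD. The largest value in the range examined is 0.23 SD, at a mean gain of 2 kg, SD 5 kg and correlation 0.5. All of these rest on assumed normality, spread and correlation, since the article gives none of them. This is a modest bias that should be corrected; the article does not support calling it decisive for the study's conclusions.

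**What to change.** Remove the weight-gain line from the exclusion criteria in section 4. State that every enrolled patient is followed, and that the main result uses all enrolled patients with a 3-month measurement. This sets the selection shift from the rule to zero by construction.

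Add two sensitivity analyses: one adjusting for weight change, and one restricted to patients whose weight changed by no more than 5 kg in either direction. Keep both secondary. Weight change may itself be affected by treatment, and the symmetric restriction is not a full remedy if mean weight change is not zero.

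The cost is one line of text and the extra analyses; weight is already collected and is due to be repeated at 3 months. Outcomes will be slightly more variable. The main before-after result also stays exposed to real weight change in both directions, which the sensitivity analyses are there to show.

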### 4.1. Sample Size

Calculation of sample size

No studies have reported on the influence of MT on the reduction in cervical fat in patients with sleep apnea and evaluations of obstruction patterns in DISE before and after. Our study will initially be a pilot study, with 15 patients in the control group, 15 patients in the moderate MT apnea group, and 15 patients with MT-CPAP severe apnea.

### 4.2. Definition of Variables

The variables that we will measure in all patients and that are reflected in the data collection table using IBM SPSS Statistics version 28 with Windows software are as follows:Age;Sex;Weight;Height;BMI;Abdominal circumference (at the level of the navel);Neck circumference (with a flexible tape on the most prominent part; for this, it is necessary for the patient to be standing, with arms hanging at the sides, head erect, and gaze forward);Measurement with IOPI of tongue force and buccinator muscle;Measurement with digital spoon (DS);Initial AHI;Ranking of velum, oropharynx, tongue base, and epiglottis (VOTE) in DISE, before and after;Ultrasound measurements: echo intensity, tongue height (mm), and tongue width (mm).

To develop the protocol, patients with sleep apnea underwent submental cervical ultrasound and DISE before starting to use the AirwayGym app (www.airwaygym.app, accessed on 27 January 2024) and after 3 months of treatment.

The AirwayGym app is a portable fitness app (Figure 2) intended for patients rather than athletes, and therapists rather than coaches provide the instructions. The novelty of this app is that it is the first healthcare app on the market that allows patients to directly interact with a smartphone without the need for any other device. The app focuses on improving proprioceptive deficits in patients with sleep apnea. When used with the app, the smartphone provides acoustic feedback on the effectiveness of the MT exercises performed [27].

The AirwayGym app comprises daily tension and concentration exercises (i.e., isometric and isotonic exercises, respectively) that can be performed anywhere. It offers the additional advantage of providing prompt feedback to allow patients to see their progress and resolve problems with the help of a therapist. Before each exercise, an animated demonstration and video provide instructions for performing the exercise. After each exercise, patients receive visual, acoustic, and tactile feedback as a score on the success of their performance. A chat function is available via which patients can contact the therapist directly. This app complies with regulations 2002/58/EC and (EU) 2016/679 regarding data protection. It is priced at EUR 8.99. Additional information can be found on the AirwayGym website.

The app presents a total of 9 myofunctional therapy exercises. Before each exercise, there is an explanatory video about them. The results of each of them are displayed with a percentage of success and are saved in an online network storage (in the cloud) and can be evaluated by a therapist. It also presents a virtual chat via which the user can communicate with a therapist.

The exercises are based on those described by Guimaraes in 2009 [21].

For hygienic reasons, we recommend covering the screen with a transparent film or cleaning the mobile screen with hydroalcoholic gel to perform the exercises [27,28].

Each of the exercises obtained from the AirwayGym website is explained below:

Exercise 1. Snake.

Stick your tongue out and press the screen with it for 5 s.

Exercise 2. Pressure with your chin.

Open your mouth and keep pushing the screen for 5 s.

While performing the exercise, say/a/.

Exercise 3. Chameleon up.

Stick out your tongue and press on the square at the bottom.

Exercise 4. Chameleon down.

Stick out your tongue and press on the square at the bottom.

Exercise 5. Tongue left cheek.

Press with the tip of your tongue the inside of the left cheek.

Contract the muscles of your cheek while pushing with the tongue toward the cheek.

Exercise 6. Tongue right cheek.

Press with the tip of your tongue the inside of the right cheek.

Contract the muscles of your cheek while pushing with the tongue towards the cheek.

Exercise 7. Pressure under chin.

Bend your head forward like you are going to drink from a cup and touch your chin on the phone.

Keep the contact and move your head from side to side for 10 s with your mouth closed.

Exercise 8. Left mandibular pressure.

Turn your jaw toward the phone and keep the pressure with your index finger on the screen for 5 s. Say/i/while performing it.

Exercise 9. Right mandibular pressure.

Turn your jaw toward the phone and keep the pressure with your index finger on the screen for 5 s. Say/i/while performing it.

DISE is performed in an operating room using a flexible endoscope and standard anesthetic monitoring of the oxygen saturation, electrocardiogram, and blood pressure. Although not mandatory, recording media (with or without audio) and playback equipment are recommended. DISE video sequences can be used for educational and research purposes or to inform patients about their test results. In our setting, an otolaryngologist will perform the endoscopic procedure, and an anesthesiologist will monitor the patients and observe their responses to medication and the procedure. Basic and advanced maneuvers (e.g., chin lift, jaw thrust, and head rotation) will be performed during DISE. The VOTE classification system is used to record the results [27,29,30,31] (Figure 3).

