Evaluation by an otorhinolaryngology specialist: The otorhinolaryngology specialist is responsible for the anatomical and functional examination of the upper airways. During this consultation, the Friedman stage and Müller maneuver are assessed, and nasofibrolaryngoscopy is performed to determine the degree of retropalatal and/or retrolingual collapse. Subsequently, functional evaluation is performed using the IOPI Medical Device to assess tongue strength by measuring the maximum pressure and tongue fatigue by measuring resistance. Low resistance values indicate a high tendency to fatigue, in which case patients would benefit from treatment modulation with the AirwayGym app.

Another instrument for measuring tongue tone is the tongue digital spoon (TDS), which has recently been applied for the diagnosis and evaluation of patients with sleep apnea and lingual hypotonia [33,34]. In addition to telemedicine follow-up, patients will be provided with a sleep diary for symptom control (Appendix C to evaluate the response and adherence to therapy with the AirwayGym app. After this consultation, the patient will be offered DISE and cervical ultrasound to optimize the selection of the current treatments for sleep apnea [35].

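### Section 4.2 lists before-and-after DISE for all patients while the group schedule in Section 2.2 gives it only to the two MT groups, and the tests named for VOTE-type data are not paired

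*Protocol article*

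**What the plan says.** The protocol article describes who has DISE in several places.

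- **Section 2.2, Study Groups.** Controls: "An initial ultrasound measurement of the tongue genioglossus fat will be made and 3 months after inclusion in this study". DISE is not mentioned for them. MT group: "An initial ultrasound measurement and drug-induced sleep endoscopy (DISE) will be performed with repeated control at 3 months". MT-CPAP group: "An initial ultrasound measurement and DISE will be made with control at 3 months".
- **Section 4.2, Definition of Variables.** The list opens with "The variables that we will measure in all patients" and includes "Ranking of velum, oropharynx, tongue base, and epiglottis (VOTE) in DISE, before and after". A sentence after the list places DISE before starting the app and after 3 months of treatment. Section 3 does the same.
- **Section 4.3, Assessments.** After the otorhinolaryngology consultation, "the patient will be offered DISE and cervical ultrasound to optimize the selection of the current treatments for sleep apnea". The visit list then has patients examined with DISE at the otorhinolaryngology visit and every initial-visit variable repeated at three months. Neither item is limited to particular groups.

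Group sizes come from Section 4.1: "with 15 patients in the control group, 15 patients in the moderate MT apnea group, and 15 patients with MT-CPAP severe apnea".

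On analysis, the end of Section 4.3 names chi-square or Fisher for categorical variables, Student's t-test or ANOVA for quantitative ones, and Mann–Whitney or Kruskal–Wallis where normality fails.

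**The concern.** An investigator following 4.2 and 4.3 would examine controls with DISE twice. One following 2.2 would not examine them at all. This is not a matter of missing detail, because two sets of statements in the same article differ on a procedure.

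The procedure is not trivial: "DISE is performed in an operating room using a flexible endoscope and standard anesthetic monitoring", with an anesthesiologist observing the response to medication. Controls are already on CPAP and do not use the app, so no stated reason requires them to have it twice.

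The second issue applies under either reading. A VOTE result before and after treatment is a pair of readings from one patient. The tests named for data of this type compare separate samples. Applied to before-after VOTE, they would treat the two readings of one patient as if they came from two patients.

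**Working it through.** **1. The sections side by side**

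| Place | Controls | MT | MT-CPAP |
|---|---|---|---|
| 2.2 | Ultrasound at both times; DISE not named | Ultrasound and DISE at both times | Ultrasound and DISE at both times |
| 4.2, variable list | VOTE before and after (all patients) | same | same |
| 3, and 4.2 after the list | Do not start the app, so not covered | DISE before the app and at 3 months | DISE before the app and at 3 months |
| 4.3, consultation | DISE offered, no group limit | same | same |
| 4.3, visit list | DISE, with initial variables repeated at 3 months; no exemption | same | same |

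The variable list in 4.2 and the visit list in 4.3 include controls by their wording. Section 2.2 leaves them out by omission, not by an explicit exclusion. Section 3 and the later sentence in 4.2 point the same way as 2.2.

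**2. Count of examinations**

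Inputs: 15 patients per group (4.1); two DISE examinations per patient (2.2 and 4.2).

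- Following 2.2: (15 + 15) x 2 = 60.
- Following 4.2 and 4.3 literally: (15 + 15 + 15) x 2 = 90.
- Difference: 90 − 60 = 30, all in controls.

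Thirty is a ceiling. Section 4.3 describes DISE as an offer, and the Discussion (5.2) says control enrolment was stopped early. The document gives neither an uptake rate nor a final control count, so the figure cannot be narrowed.

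**3. Paired data and the tests named**

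Chi-square, Fisher, Mann–Whitney and Kruskal–Wallis all assume independent observations. To see what ignoring the pairing does, take an assumed example: one group of 15, with a site collapsed in 12 before and 6 after.

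Fisher uses only these margins, the table [[12, 3], [6, 9]], and gives two-sided p = 0.060. The exact McNemar test depends on how many patients improved (b) and worsened (c). The margins fix b − c = 6. At most 3 patients can worsen, since only 3 started without collapse. With c the smaller count, two-sided p = 2 x Σ(k = 0 to c) C(b + c, k) / 2^(b + c):

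| b / c | Calculation | Exact McNemar p | Fisher p |
|---|---|---|---|
| 6 / 0 | 2 x 1/64 | 0.031 | 0.060 |
| 7 / 1 | 2 x 9/256 | 0.070 | 0.060 |
| 8 / 2 | 2 x 56/1024 | 0.109 | 0.060 |
| 9 / 3 | 2 x 299/4096 | 0.146 | 0.060 |

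The paired p-value is smaller in one pairing and larger in three. The independent-sample test cannot tell these four situations apart. That is the defect; the example does not show in which direction the trial's own result would move. It also reduces VOTE to collapsed or not, whereas the protocol records a ranking.

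**The case against.** The strongest reply is that the intent is clear enough. Section 2.2 is the only group-by-group schedule, and a specific schedule normally governs a generic list. DISE is tied to the app in Section 3 and again in 4.2, so before and after most naturally means before and after MT. Section 4.3 is loosely worded in any case: it has patients in all three groups monitored for treatment with an app that controls do not use. Its list of assessments after MT does not name DISE at all. Figure 1, cited for the group schedule, is not shown and may settle the matter.

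Much of this stands. It makes 2.2 the probable intent and sets the direction of the fix. It does not remove the all-patients wording from 4.2, which would need correcting even if Figure 1 agreed with 2.2.

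On the tests, one can say that the list is short and generic, assigns no test to VOTE change, and leaves details to an analysis plan. It is true that no sentence says Fisher or Mann–Whitney will compare a patient's two readings. But the article does state which tests serve categorical and non-normal variables. VOTE before and after is one of its listed variables, and none of those tests fits it.

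Three stronger readings are tempting, and the documents support none of them:

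- **That the trial commits controls to 30 drug-induced examinations.** DISE is offered, control enrolment stopped early, and the weight of the text favours 2.2.
- **That a planned control comparison of VOTE is lost.** No section plans one. It would in any case be confounded by severity and CPAP, since the groups are not randomized.
- **That the unpaired tests would miss a real effect.** As the table shows, the direction of the difference depends on the within-patient pairing.

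**Conclusion.** The inconsistency is real and should be corrected. Section 4.2, with no exemption in 4.3, assigns before-and-after DISE to everyone; Section 2.2 assigns it to two of three groups and is the more likely intent. At most 30 examinations in 15 controls depend on which section is followed. That ceiling assumes full control enrolment and full uptake of both examinations.

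The mismatch between paired VOTE data and the independent-sample tests named also holds, whichever group reading is right. No particular p-value shift should be claimed for it.

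**What to change.** **Schedule.** Limit the VOTE/DISE item in 4.2, and the DISE offer, examination and three-month repeat in 4.3, to the MT and MT-CPAP groups. If control DISE is intended, add it to the control paragraph of 2.2 at inclusion and 3 months, alongside the ultrasound.

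**Analysis.** Analyse before-after VOTE change within each group with a paired ordinal test, for example Wilcoxon signed-rank per site, and report it as descriptive. Without control DISE the change is uncontrolled; with it, any comparison between groups remains confounded.

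**Cost.** A few wording changes and one named test. The preferred option adds no procedure and spares controls one. Its price is that controls then contribute nothing to the Section 2.3 objective on whether ultrasound plus DISE changes the surgical indication compared with DISE alone. That objective is not restricted to MT patients, so up to 15 of 45 patients drop out of it. The article should say so.
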